## Study design

This is a prospective, single-center, three-arm parallel randomized controlled trial. Patients will be randomly assigned to three groups: (1) tDCS+MNS group: receiving real tDCS and MNS treatment; (2) Sham tDCS+MNS group: receiving sham tDCS and real MNS treatment; (3) tDCS+Sham MNS group: receiving real tDCS and sham MNS. Each group will consist of 27 patients, with treatment lasting for 4 weeks (22).

Randomization will be implemented using a web-based central randomization system, developed by an independent statistician using the “blockrand” package in R software (version 4.1.0) (23). We will employ a stratified randomization strategy to ensure balanced baseline characteristics across groups. Randomization will be stratified by age (≤50 years/>50 years) and baseline consciousness level (vegetative state/minimally conscious state) (9). The allocation ratio will be 1:1:1, using variable block sizes (4 or 6) to enhance allocation unpredictability. To ensure allocation concealment, the randomization sequence will be stored in the central randomization system, and the study coordinator will only obtain the allocation result through this system after the patient has completed all baseline assessments and confirmed eligibility. The system will send the allocation result to the therapist responsible for implementing the intervention via encrypted email.

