### Sample size

Sample size calculation was performed using the Coma Recovery Scale-Revised (CRS-R) score as the primary outcome measure. We employed a one-way analysis of variance (ANOVA) model to determine the required sample size (25). Calculations were conducted using G*Power software (version 3.1.9.7, University of Düsseldorf, Germany) (26).

Based on previous similar studies (14, 27), we assumed a clinically significant difference of 4 points in CRS-R scores between the treatment and control groups. This threshold is based on previous research by Estraneo et al. (24), which demonstrated that a 4-point change in CRS-R score is associated with meaningful transitions between diagnostic categories and correlates with clinically observable improvements in patient responsiveness and function, with a standard deviation of 7.3 points. The significance level (*α*) was set at 0.05, and the power (1-*β*) at 0.8, which are commonly used parameters in clinical trials (28).

For a 3 × 6 mixed repeated measures ANOVA (one 3-level between-subjects factor and one 6-level within-subject factor), G*Power calculated a required sample size of 22 participants per group to detect a medium effect size (*f* = 0.25) with 80% power at a 5% significance level, considering correlations among repeated measures of 0.5 and a nonsphericity correction of 0.75. To account for potential dropouts and loss to follow-up, we increased the sample size by 20% (19, 29). Consequently, the final sample size was determined to be 27 participants per group, totaling 81 participants for the three-group study design.

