#### Statistical methods

(1) Descriptive statistics: Continuous variables will be presented as mean ± standard deviation (for normally distributed data) or median and interquartile range (for non-normally distributed data); categorical variables will be presented as frequencies and percentages.

(2) Between-group comparisons: Baseline characteristics: Continuous variables will be compared using one-way analysis of variance (ANOVA) (for normally distributed data) or Kruskal-Wallis test (for non-normally distributed data); categorical variables will be compared using chi-square test or Fisher’s exact test.

(3) Primary outcome analysis: First, within-group comparisons will be conducted to assess changes in CRS-R scores from baseline to each follow-up time point within each intervention group. Paired t-tests (for normally distributed data) or Wilcoxon signed-rank tests (for non-normally distributed data) will be used for these comparisons. This will provide insights into the therapeutic effectiveness of each intervention approach. Subsequently, between-group comparisons will be performed using a 3 × 6 mixed repeated measures analysis of covariance (ANCOVA) with group (tDCS+MNS, sham tDCS+MNS, and tDCS+sham MNS) as a between-subjects factor and time (baseline, 4 weeks post-treatment, and follow-ups at 2 weeks, 4 weeks, 12 weeks, and 24 weeks) as a within-subjects factor. To control for potential confounding variables, baseline age, sex, duration of consciousness disorder, and baseline severity will be included as covariates if significant differences are observed at baseline despite randomization. Post-hoc analyses with appropriate multiple comparison corrections will be used to identify specific group differences at each time point. The analysis will include all assessment time points (baseline, 4 weeks post-treatment, and follow-ups at 2 weeks, 4 weeks, 12 weeks, and 24 weeks) (40). If data violate normality assumptions, generalized estimating equations (GEE) models will be employed (41).

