(4) Secondary outcome analyses: For continuous secondary outcomes (e.g., fNIRS, EEG, and ERP metrics), both within-group and between-group analyses will be conducted following the same approach as the primary outcome. Within-group changes will be assessed first, followed by between-group comparisons with appropriate covariate adjustments. Categorical secondary outcomes (e.g., GOS-E) will be analyzed using ordinal logistic regression, with baseline measurements included as covariates to account for potential confounding.

(5) Missing data handling: Multiple imputation techniques will be used to handle missing data, reducing bias and improving statistical power, The imputation model will include all primary and secondary outcomes, as well as key baseline covariates (age, sex, time since injury, baseline CRS-R score, and consciousness state). We will generate 20 imputed datasets, as recommended by methodological guidelines (42); Results will be pooled using Rubin’s rules, and sensitivity analyses will include complete case analysis to assess the impact of missing data on results.

(6) Subgroup analyses: Pre-specified subgroup analyses will be conducted based on age, sex, duration of consciousness disorder, and baseline CRS-R scores to explore potential effect modifiers. To control for multiple comparisons in these subgroup analyses, we will apply the same Bonferroni correction approach used for secondary outcomes. Furthermore, we will clearly label these analyses as exploratory and interpret the results with appropriate caution regarding potential Type I error inflation.

(7) Sensitivity analyses: In addition to ITT analysis, PP analysis will be performed to evaluate treatment effects in patients who fully adhered to the protocol.

(8) Covariate handling: Despite our stratified randomization strategy, potential imbalances in baseline characteristics might still exist. Therefore, we will compare baseline demographic and clinical characteristics between groups. If any significant differences are detected (*p* < 0.05), these variables will be treated as covariates in subsequent analyses to minimize confounding. Additionally, baseline measurements of outcome variables will routinely be included as covariates in the respective analyses to account for potential regression to the mean effects and to increase statistical power.

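### Apart from baseline outcome values, covariates are chosen by baseline significance tests, the stratification factors are not fixed in the primary model, and baseline CRS-R has conflicting roles

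*Protocol article*

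**What the plan says.** All references are to the Protocol article.

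- **Statistical methods, item (3).** The primary analysis is a 3 × 6 mixed repeated measures ANCOVA. Age, sex, duration of the consciousness disorder and baseline severity "will be included as covariates if significant differences are observed at baseline despite randomization". The within-subject factor includes baseline: "and time (baseline, 4 weeks post-treatment, and follow-ups at 2 weeks, 4 weeks, 12 weeks, and 24 weeks) as a within-subjects factor".
- **Statistical methods, item (8).** Baseline characteristics are compared between arms. If any differ at p < 0.05, "these variables will be treated as covariates in subsequent analyses to minimize confounding". The same item then makes an exception: "baseline measurements of outcome variables will routinely be included as covariates in the respective analyses".
- **Study design.** "Randomization will be stratified by age" (50 or below against above 50) and by vegetative against minimally conscious state (VS/MCS). "The allocation ratio will be 1:1:1".
- **Where the strata appear in the analysis.** Age is a conditional covariate in item (3). Consciousness state is named only in the imputation model, item (5). Neither is a fixed term of the primary model.

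**The concern.** There are three linked problems.

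1. **The screen.** When allocation is random, a baseline difference between arms is chance. A significance test therefore says nothing about whether a variable predicts CRS-R. A strong predictor that happens to be balanced stays out, and an irrelevant one that happens to be imbalanced goes in. The primary model is not known until the baseline tests have been run.
2. **Baseline CRS-R.** Item (3) makes baseline severity conditional, while item (8) makes the baseline value of the outcome routine. If severity means CRS-R, two analysts following the two items would fit different primary models. Baseline is also one of the six outcome levels.
3. **The strata.** The trial constrains allocation on age group and VS/MCS, then admits them to the model only if they differ significantly, which stratification is there to prevent. If the strata are prognostic, the model's standard errors for a group contrast are too large.

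At stake are precision, correctly calibrated tests at single visits, and a primary model that is fixed in advance.

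**Working it through.** **1. The plan's own figure.** Sample size asks for f = 0.25, "with 80% power at a 5% significance level" and nonsphericity correction 0.75, with 3 groups and 6 times. For the group-by-time interaction at N = 66:
- df1 = 2 × 5 × 0.75 = 7.5
- df2 = 63 × 5 × 0.75 = 236.25
- λ = f²·N·(m−1)·ε = 0.0625 × 66 × 5 × 0.75 = 15.47

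Power is 0.810, against 0.787 at N = 63, so 22 per group reproduces. Then 22 × 1.2 = 26.4, rounded up to 27 per group. The figure is not disputed here. It matters because the stated size matches the interaction test (see step 6).

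**2. How often the screen opens.** Four independent tests at 0.05 give 1 − 0.95⁴ = 0.185; three give 1 − 0.95³ = 0.143. In the simulation of step 5, with the age stratum balanced by stratified allocation, at least one of the four variables flagged in about 12–16% of trials. Item (8) has no closed list of variables, so its own rate cannot be computed.

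**3. Baseline CRS-R, side by side.** Item (3): severity enters if significant. Item (8): baseline outcome enters always. Item (3) again: baseline is an outcome level. If all are applied, then at the baseline level the outcome equals its own covariate. A common slope then averages one visit where it is exactly 1 with five visits where it is something else.

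**4. Omitted strata, single visit.** Let R² be the share of the remaining outcome variance that the balanced strata explain. The true variance of a contrast is (1 − R²) times what the model assumes. In large samples:
- pairwise test size = 2·[1 − Φ(1.96/√(1 − R²))]: 0.039 at R² = 0.10, 0.024 at 0.25, 0.019 at 0.30
- three-arm 2-df test size = 0.05^(1/(1 − R²)): 0.036 at 0.10, 0.024 at 0.20, 0.014 at 0.30

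**5. Simulation, single visit.** Inputs from the protocol are 27 per arm, SD 7.3 and a 4-point gain, here in the combined arm only. Assumptions are the R² values, blocks of 3 within strata, and strata independent of baseline CRS-R. The test is the 2-df group F test, with 4,000 null and 2,000 alternative runs. Models: (a) screened covariates only; (b) baseline CRS-R always in, plus screened covariates, as item (8) reads; (c) baseline CRS-R and both strata always in.

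| R² strata / baseline | Power (a) | Power (b) | Power (c) | Type I (a) | Type I (b) | Type I (c) |
|---|---|---|---|---|---|---|
| 0.10 / 0.25 | 0.51 | 0.63 | 0.71 | 0.028 | 0.034 | 0.052 |
| 0.20 / 0.25 | 0.50 | 0.66 | 0.79 | 0.019 | 0.019 | 0.053 |
| 0.20 / 0 | 0.50 | 0.50 | 0.62 | 0.023 | 0.024 | 0.047 |
| 0.10 / 0.50 | 0.52 | 0.84 | 0.91 | 0.026 | 0.028 | 0.057 |

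Monte Carlo standard errors are about √(0.05 × 0.95/4000) = 0.003 for size and at most √(0.25/2000) = 0.011 for power. No adjustment at all gives power 0.50–0.51, so the screen alone adds essentially nothing. From (b) to (c) the gain is 6 to 13 points (0.844 to 0.906; 0.658 to 0.792). In the first row the standard error of a pairwise contrast falls from 1.98 to 1.74 to 1.61.

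**6. Does this reach the interaction?** A stratum effect that is the same at every visit belongs to the patient's mean level and drops out of within-patient comparisons. A simulation with six visits, 27 per arm, omitted strata explaining 30% of variance and 5,000 null runs gave size 0.050 for the interaction and 0.014 for a single visit. The latter agrees with step 4.

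**The case against.** Several stronger readings are tempting, and the documents do not support them.

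- **That baseline CRS-R is usually left out.** From item (3) alone, a reader might infer that it is omitted in about 95% of trials and that fixing this lifts pairwise power from 51% to 63%. Item (8) includes baseline outcome values routinely, so that gain is already planned. Even under item (3) alone, baseline is used through the time factor, and the primary outcome is change from baseline. Against a change score with 27 per group, the gain from baseline adjustment depends on an assumed correlation: 0.51 to 0.63 at 0.5, 0.72 to 0.79 at 0.7, 0.88 to 0.91 at 0.8.
- **That 18.5% is the expected rate.** It treats stratified variables as free tests, so it is an upper figure for the four named variables.
- **That the primary test runs at about 2%.** That applies to group contrasts at one visit under an assumed R². It does not apply to the interaction when stratum effects are constant over time.
- **That 6–13 points is the expected loss.** VS/MCS is diagnosed with the CRS-R (Inclusion criteria, item 2), so adjusting for baseline CRS-R already captures part of what that stratum explains. The simulation ignores this overlap.
- **That the analysis is steered by results.** The rule is stated in advance and uses baseline data only, and analysts see coded groups. No inflation of false positives is shown; the error is conservative.

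It can also be said that stratum terms may be left to an analysis plan that is not shown. That would answer silence. Here the protocol states a rule, and it makes age, and under item (8) any other baseline variable except the outcome's own baseline value, conditional on significance.

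These objections limit the size of the point. They leave standing the chance-based screen, the conflict over baseline CRS-R and the absence of fixed strata.

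**Conclusion.** The concern holds in limited form. Items (3) and (8) choose covariates by chance imbalance. The chance of at least one flag among the four named variables is at most 18.5% if the tests are independent, and about 12–16% with the age stratum balanced. Items (3) and (8) conflict on baseline CRS-R if severity means CRS-R, and using baseline also as a level of time leaves the model incoherent.

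Omitting the strata makes between-group contrasts at single visits conservative and less precise if the strata are prognostic. With baseline CRS-R in the model, type I error is about 0.02–0.03 against a nominal 0.05, and the power loss is 6–13 points as an upper range. Both rest on R² values that are not in the documents. The effect is smaller where baseline CRS-R already carries the VS/MCS information, and it does not extend to the group-by-time interaction under time-constant stratum effects. The direct consequence falls on the planned post-hoc comparisons at each time point, and on any week-4 contrast used for the stated primary outcome.

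**What to change.** 1. Delete the significance rule for covariates in Statistical methods items (3) and (8).
2. State that the primary model and the models for continuous secondary outcomes always include the baseline value of the outcome, age stratum (50 or below, above 50) and VS/MCS stratum, whatever the baseline balance.
3. Let the time factor cover post-baseline visits only, with baseline as a covariate. The group-by-time term then no longer contains the change from baseline, so name the group contrast that answers the primary question, and bring the 3 × 6 description under Sample size into line.
4. Report baseline characteristics descriptively, without p-values.

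The cost is wording only. Age, consciousness state and baseline CRS-R are already collected, and no visit or procedure changes.

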### Outcome measures

#### Primary outcome measure

The primary outcome measure is the change in total score on the Coma Recovery Scale-Revised (CRS-R) from baseline to post-treatment (24). The CRS-R is the gold standard for assessing patients with disorders of consciousness and comprises six subscales: auditory, visual, motor, oromotor, communication, and arousal, with a total score range of 0–23 (32). CRS-R assessments will be conducted by trained evaluators at baseline, after 4 weeks of treatment, and at 2 weeks, 4 weeks, 12 weeks, and 24 weeks post-intervention. To ensure consistency and accuracy, all evaluators will undergo standardized training and pass a video scoring test to ensure inter-rater reliability (ICC > 0.8) (24).

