All statistical analyses will be conducted using R software (version 4.1.0 or higher), with a significance level set at *α* = 0.05 (two-sided). To control for Type I error inflation due to multiple comparisons, Bonferroni correction will be applied to adjust *p*-values for secondary outcomes (43).

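### Switching the CRS-R analysis to GEE when data look non-normal cures nothing at 27 per arm, and in its usual form runs the joint group-by-time test at about 14–15%

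*Protocol article*

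**What the plan says.** In the Protocol article, Statistical methods, item (3), the between-group analysis of CRS-R is a mixed repeated-measures ANCOVA with three groups and six time points, baseline included. Post-hoc comparisons at each time point follow, with a multiplicity correction that is not named. The same item then sets a rule for changing method: "If data violate normality assumptions, generalized estimating equations (GEE) models will be employed". It names no link, variance estimator or reference distribution for the GEE.

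Item (8) of the same section also makes the baseline value of each outcome a routine covariate. The significance level is 5%, two-sided.

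Under Sample size, the calculation gives "a required sample size of 22 participants per group to detect a medium effect size (*f* = 0.25) with 80% power", "considering correlations among repeated measures of 0.5 and a nonsphericity correction of 0.75", and after the allowance for dropout "the final sample size was determined to be 27 participants per group, totaling 81 participants for the three-group study design". Under Primary outcome measure, the endpoint is the change in CRS-R total from baseline to the end of treatment, on a scale "with a total score range of 0–23". The analysis set is all randomised patients, with multiple imputation of missing data.

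**The concern.** CRS-R is a bounded integer score measured here in vegetative and minimally conscious patients, so a normality check could well fail and trigger the switch. GEE with an identity link fits the same group-by-visit means as the model it replaces. What changes is the variance and the test. The robust variance is justified by a large number of patients, and this trial has 27 per arm. The replaced F test is known to tolerate moderate skewness at such sizes. The rule may therefore swap a test that works for one that does not.

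The choice of test also depends on the outcome data. If the two candidate tests have different error rates, the rule as a whole has no stated error rate. At stake is a group-by-time p-value that overstates the evidence for a difference between three arms that all receive at least one real stimulation.

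**Working it through.** **Inputs from the article.** Three arms, six assessments, 27 per arm, two-sided 5%, scores 0–23, all randomised patients analysed.

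**Assumed, with the range shown.** Compound symmetry with correlation 0.5 (the value used for sizing) and AR(1) with 0.55, 0.70 and 0.85; normal, lognormal, t with 3 df, and skewed or clipped integer 0–23 scores; identity link, full group × visit mean model, complete data.

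**1. The plan's own figure.** For the group-by-time F test, df1 = (3−1)(6−1)(0.75) = 7.5. At N = 66, df2 = (66−3)(5)(0.75) = 236.25. With noncentrality f²·N·(6−1)·ε = 0.0625 × 66 × 5 × 0.75 = 15.47, power is 0.810, so 22 per group reproduces. Then 22 × 1.2 = 26.4, rounded up to 27, and 3 × 27 = 81. Other forms do not return 22: the noncentrality that uses the 0.5 correlation gives 10 per group, and the between-groups test gives 31. The group-by-time test is thus the one that best matches the stated size.

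**2. Degrees of freedom.** Joint group-by-time test: (3−1)(6−1) = 10. With baseline as a covariate only and five later visits: (3−1)(5−1) = 8.

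**3. The usual GEE test.** Let d hold the 10 differences between arms in five orthonormal time contrasts, and let S be the robust covariance of d, built from each arm's residual cross-products divided by n². The test rejects if d′S⁻¹d exceeds the 95th percentile of chi-square with 10 df. Each arm contributes its own 5 × 5 covariance, with 5 × 6 / 2 = 15 distinct elements, estimated from 27 patients.

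**4. Rejection rates under a true null, 27 per arm** (range over the five score distributions):

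| Test | Compound symmetry 0.5 | AR(1) 0.70–0.85 |
|---|---|---|
| GEE robust, chi-square Wald, 10 df | 0.130–0.152 | 0.120–0.147 |
| GEE, Mancl-DeRouen variance, chi-square | 0.096–0.114 | 0.088–0.113 |
| GEE, Mancl-DeRouen variance, F-type reference | 0.033–0.048 | 0.031–0.048 |
| GEE score test | 0.028–0.040 | 0.026–0.039 |
| GEE, model-based exchangeable variance | 0.058–0.066 | 0.082–0.113 |
| GEE robust, single contrast (1 df) | 0.051–0.060 | 0.055–0.063 |
| Repeated-measures ANOVA, uncorrected | 0.044–0.051 | 0.068–0.098 |
| Repeated-measures ANOVA, Greenhouse-Geisser | 0.031–0.047 | 0.038–0.053 |

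**5. Larger run, 20,000 replicates per setting.** These use compound symmetry 0.5 and AR(1) 0.55 (ε about 0.7, close to the 0.75 used for sizing). The Monte Carlo standard error at 0.148 is √(0.148 × 0.852 / 20,000) = 0.0025.
- GEE robust Wald, 10 df: 0.149 (normal) and 0.146 (skewed 0–23) under compound symmetry; 0.148 and 0.148 under AR(1). That is about three times 0.05.
- GEE robust Wald, 8 df: 0.115–0.124.
- ANOVA on the same 10-df data: uncorrected 0.048–0.050 under compound symmetry and 0.071–0.073 under AR(1); Huynh-Feldt 0.046–0.051 throughout.
- The Abstract gives 138 patients, which conflicts with 81. At 138 / 3 = 46 per arm, GEE would still run at 0.098–0.101.

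**6. Reading.** Normal and skewed 0–23 scores give the same inflation, so skewness is not the cause. The cause is inverting a 10-dimensional covariance estimated from few patients. A variance correction alone does not restore the level; it needs an F-type reference as well.

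**The case against.** The strongest reply is that the 14–15% belongs to a test the article never specifies. Variance estimator and reference distribution are commonly left to a statistical analysis plan, and they decide the answer: corrected variance with an F-type reference, or a score test, holds 5% or less. This stands. A reader might infer that following the rule makes the main test of the trial run at 15%; the article does not fix enough to support that. What the article does fix is the switch itself, and an analysis plan that follows it would inherit it.

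A second reply is that the inflated test is not the primary contrast. The primary outcome is the week-4 change, and single GEE contrasts run at about 6%. A null simulation of the stated sequence used uncorrected GEE variance, 6,000 replicates per scenario, and Bonferroni as an assumption for the unnamed correction. Some pairwise week-4 difference appeared in 5.5–6.3% of trials. A significant joint test together with a corrected pairwise difference at any visit appeared in 3.7–4.5%. So the inference that a false arm difference would be declared in 15% of trials is not supported either. Only the joint p-value, read alone, is affected to that degree.

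Third, the ANCOVA is not safe as written. The analysis section repeats no sphericity correction, although the sizing assumed 0.75, and the uncorrected test reaches about 7–10% when sphericity fails. This also stands, and the fix has to deal with it.

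Finally, rates of 16–18% arise at 22 per arm, but all 27 randomised per arm are to be analysed with imputation, so that is not the planned analysis.

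**Conclusion.** The point holds in limited form. The switch to GEE does not address non-normality. In the usual GEE form it raises the joint group-by-time test from about 5% (ANOVA with sphericity or a correction) to about 14–15% at 27 per arm, or 11–12% on 8 df. Heavy-tailed or lognormal data bring the 10-df figure to 12–14%. The week-4 contrasts are affected only slightly, at about 6%.

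The large figure requires uncorrected robust variance, a chi-square Wald reference and use of the joint test. The correlation patterns and score distributions are assumptions, and pooling over imputed data sets was not simulated. How often the switch would be triggered cannot be judged from the article. It is worth correcting because the rule is stated, depends on the outcome data, and brings no gain in the settings examined.

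**What to change.** Remove the switch in Statistical methods, item (3). Pre-state one model to be used whatever the residual shape:

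- either the repeated-measures model with a Greenhouse-Geisser or Huynh-Feldt correction, or a likelihood-based model with unstructured covariance and small-sample degrees of freedom;
- the between-group contrasts in week-4 change as the primary test, which matches the defined primary outcome.

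If GEE is kept, label it a sensitivity analysis and specify bias-reduced variance with a t or F reference, or a score test. If a distribution-free check is wanted, add a re-randomisation test of the week-4 contrasts that respects the randomisation strata (age and consciousness level).

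The cost is protocol or analysis-plan wording and a few lines of code. Patients, visits and sample size do not change. The downside is that there is no automatic fallback for non-normal data and slightly more analysis work; the simulations give no sign that the fallback is needed for skewed 0–23 scores.

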#### Study safety

Based on previous research, transcranial direct current stimulation and median nerve stimulation are considered relatively safe, non-invasive techniques (16). However, we will closely monitor potential adverse events, including but not limited to: (1) mild discomfort, redness, or itching at the stimulation site; (2) transient headache or dizziness; (3) nausea; (4) fatigue. To address these potential adverse events, we have developed a detailed response plan: (1) All research personnel will receive training in adverse event identification and management. (2) Given that patients with prolonged disorders of consciousness (pDoC) cannot reliably self-report subjective adverse events, a comprehensive monitoring approach has been implemented, including systematic observation of objective signs (skin reactions, autonomic changes such as heart rate, blood pressure, and sweating, facial expressions, and behavioral responses); physiological parameter monitoring (temperature, blood pressure, and heart rate before and after each session); neurophysiological indicators (EEG changes during treatment and follow-up that may indicate discomfort or adverse responses); caregiver reports (detailed inquiries to family members and caregivers about any unusual behaviors or responses); and clinical judgment (comprehensive assessment by experienced clinicians familiar with detecting subtle signs of discomfort in non-communicative patients). (3) Detailed assessments using the above methods will be conducted before and after each treatment session and at all follow-up visits. (4) Any identified adverse events will be documented and evaluated by a physician not involved in the direct treatment delivery. (5) For adverse events management, we will implement a standardized classification system based on the Common Terminology Criteria for Adverse Events (CTCAE v5.0). All adverse events will be graded on a 5-point scale (1: mild; 2: moderate; 3: severe; 4: life-threatening; 5: death-related) and systematically documented in a dedicated adverse event log. Events of grade 3 or higher will be reported to the ethics committee within 24 h.

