### Statistical analysis

#### Analysis principles

This study will employ intention-to-treat (ITT) analysis as the primary analytical approach to evaluate the efficacy of transcranial direct current stimulation combined with median nerve stimulation in patients with chronic disorders of consciousness (38). The ITT analysis will include all randomized patients, regardless of protocol adherence or treatment completion. Additionally, we will conduct a per-protocol (PP) analysis as a supplementary measure to assess treatment effects in patients who fully adhered to the study protocol (39).

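### Taken literally, the missing-data rule imputes living CRS-R scores after a patient's death, so the follow-up CRS-R comparisons could hide a mortality difference between arms

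*Protocol article*

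**What the plan says.** All references are to the Protocol article.

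- **Missing data.** Statistical methods (5) fixes the approach: "Multiple imputation techniques will be used to handle missing data, reducing bias and improving statistical power". On content, "The imputation model will include all primary and secondary outcomes, as well as key baseline covariates"; the covariates listed are age, sex, time since injury, baseline CRS-R and consciousness state. Survival status is not listed. Twenty imputed datasets are pooled by Rubin's rules.
- **Sensitivity.** For missing data, "sensitivity analyses will include complete case analysis to assess the impact of missing data on results". Item (7) adds only a per-protocol analysis.
- **Population.** Analysis principles: "The ITT analysis will include all randomized patients, regardless of protocol adherence or treatment completion".
- **Outcome and model.** "The primary outcome measure is the change in total score on the Coma Recovery Scale-Revised (CRS-R) from baseline to post-treatment", "with a total score range of 0–23". Statistical methods (3) tests it in a 3 × 6 model over baseline and Weeks 4, 6, 8, 16 and 28 (weeks as in Table 1), with post-hoc group comparisons at each time point.
- **Death.** It appears only in the adverse-event grading under Study safety: "4: life-threatening; 5: death-related". No sentence says how a death enters any efficacy analysis.

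**The concern.** Take a patient who dies at Week 12. The CRS-R scores at Weeks 16 and 28 are then absent. The stated rule fills them from baseline data, earlier scores and the other outcomes, so the patient enters the ITT analysis with plausible living values. A score after death is not an unobserved value that better follow-up could have recovered, and a model fitted to survivors' scores has no information about it.

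Complete case does not repair this, because it removes the patient. In a repeated-measures ANOVA that needs all six values, it also discards that patient's observed Week 4 score. One analysis replaces the death with a living score and the other deletes the patient, so agreement between them would say nothing about the effect of deaths. What is at stake is the long-term CRS-R result. The Introduction and Discussion name long-term efficacy over six months as an aim, and the later visits feed the group-by-time test.

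**Working it through.** **The plan's own figures.** There is no mortality figure to reproduce. The arm size follows from the Sample size section: 22 × 1.2 = 26.4, rounded up to 27 per group. The same section gives the 4-point CRS-R difference used below as a yardstick.

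**Assumed inputs (not in the article).**
- Deaths by Week 28: 3% to 15% per arm, that is 27 × 0.03 = 0.8 to 27 × 0.15 = 4.1 patients.
- Mean CRS-R among survivors, and hence mean imputed score: 10 in both arms, varied from 8 to 12.
- Score given to a death when it is counted as the worst result: 0, the bottom of the scale.

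**Formula.** With n per arm, deaths dA and dB, and imputed mean m:

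shift in arm difference = (dA − dB) × m / n

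**Example: 4 deaths in arm A, 2 in arm B, m = 10, n = 27.**

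| Handling of deaths | Arm A mean | Arm B mean | A − B |
|---|---|---|---|
| Imputed as living | 10 | 10 | 0 |
| Complete case (23 and 25 patients) | 10 | 10 | 0 |
| Scored 0 | 10 × 23/27 = 8.52 | 10 × 25/27 = 9.26 | −0.74 |

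Check: (4 − 2) × 10 / 27 = 0.74 points, and 0.74 / 4 = 18.5% of the planned difference. Both analyses named in the plan return about zero.

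**Range.**
- m = 8: 2 × 8 / 27 = 0.59 points. m = 12: 2 × 12 / 27 = 0.89 points.
- Expected death rates of 15% versus 5%, m = 10: (0.15 − 0.05) × 10 = 1.0 point. A simulation with 27 per arm and an SD of 5 among survivors gave −1.01 with deaths scored 0 and −0.01 from survivors only.
- Equal deaths in the two arms and equal imputed means: shift 0.

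**Which visits are exposed.** A death affects only the visits after it. The Week 4 score is exposed only to deaths within the four treatment weeks. Weeks 16 and 28 carry the accumulated deaths and are the most exposed.

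**The case against.** **Left to the analysis plan.** The missing-data item never mentions death. On a careful reading a score after death is not missing data at all, and the sensitivity analyses are not presented as an exhaustive list. This is a condensed article, and the handling of deaths is often set out in an analysis plan that is not shown. That could resolve the point. It does not remove it, because the article goes beyond silence: it fixes a method, lists the model's variables, keeps all randomized patients and names the check. Applied as written, these produce the result described.

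**GOS-E.** A reader might infer that no efficacy outcome counts death and that GOS-E is also imputed to a living category. The article does not support this. GOS-E has a lowest category for death, so a known death is an observed value, and the ordinal regression in Statistical methods (4) would count it as the worst result. Nothing says that it is missing or imputed. The safeguard is limited, since GOS-E is secondary and in Table 1 is last measured at Week 16.

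**Deaths may be few or balanced.** Entry requires age 18–65, stable vital signs, no ventilation and a stable CRS-R. The grade 5 entry is simply the top of a standard grading scale and does not show that deaths are expected. No statement suggests that mortality differs by arm. All of this stands, and it limits the likely size.

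**No single correct target.** The 0.74 points is the gap between two ways of treating death, not a bias against one agreed estimand. That also stands. The plan needs to say which one it means.

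**Conclusion.** The point holds for CRS-R at the follow-up visits. Read literally, the plan gives patients who die living scores at later visits, and its named check drops them, so a mortality difference between arms could go unseen in the long-term CRS-R comparisons.

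A reader might go further and infer that the primary result itself is compromised. The documents do not support that: the defined primary outcome is the change to Week 4, which is little affected, although the 3 × 6 model does bring in the later visits.

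The size rests wholly on assumed mortality. It is about 0.74 points with 4 versus 2 deaths of 27 and an imputed mean of 10, about 1 point at 15% versus 5%, and none if deaths are balanced.

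**What to change.** In Statistical methods (5), before unblinding:

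1. State that CRS-R at visits after death is not imputed as ordinary missing data, and say what the follow-up comparison then estimates. If it is limited to patients alive at the visit, acknowledge that this conditions on survival after randomization and departs from the all-randomized ITT principle.
2. Add a sensitivity analysis that keeps all randomized patients and gives deaths the worst rank (CRS-R score 0) from the date of death.
3. Confirm that death is scored in the lowest GOS-E category and is not imputed.
4. Record all-cause death with its date. Secondary outcome measures (6) lists only treatment-related adverse events, and Study safety, though broader, does not mention the date of death.
5. Report deaths by arm beside each follow-up CRS-R result.

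The cost is a few sentences, one data field and one extra analysis. The long-term estimate may come out less favourable.
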